**Fig 1 pone.0278746.g001:**
[figure not shown]
Showing the trials schedule of enrolment, interventions and assessments.

Participants will be recruited via advertisements emailed to schools, shared via social media and word of mouth. Participants and their parents/carers will be sent an electronic information sheet and given the opportunity to ask any questions before completing an online consent form. Participants will provide informed ascent as they are under 18, with parents/carers providing informed consent. Participants and their parents/carers will then complete a baseline eligibility assessment. They will complete a range of online questionnaires via Qualtrics [41], a secure online platform. They will then attend a remote research assessment appointment to determine whether the family meet the eligibility criteria. The researcher completing the baseline and post-intervention assessments will not be involved in the clinical intervention and will be blinded to baseline allocation. After all baseline assessments for the participant group are completed, they will be discussed within supervision to confirm that the participants meet eligibility criteria. Eligible participants will then be randomised using a random number generator to one of four different baseline lengths (12 days, 19 days, 26 days or 33 days [42]. The decision to have a minimum of 12 observations per phase meets the requirements for guidelines and standards [43] and will allow for sufficient power for Tau-U analysis [44, 45].

Each of the families will then be contacted to inform them of their allocation. Randomisation and contacting of the families will be completed by a third researcher, who is not involved in either the clinical intervention or research assessments. Families will receive a £25 voucher for completing the baseline eligibility assessment. A letter will also be sent to their General Practitioner (GP) informing them of the family’s participation in the research study. The setting for the entire study will be remote via Zoom [46], with participants recruited from across the United Kingdom (UK).

All participants in the group will begin their baseline phase concurrently. During the baseline phase participants will be asked to complete the Three-Item Loneliness Scale [34] each day via Qualtrics [41]. SMS message reminders will also be sent to the young people and their parent/carers each day.

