The baseline phase will be immediately followed by the intervention. Each family will receive (on average) 12 sessions of CBT for loneliness in children and young people. Where possible the first 4 sessions will take place bi-weekly, the second 4 sessions weekly and the final 4 sessions fortnightly.

For all participants the first two sessions will be focussed on assessment and then formulation. The final session for all participants will focus on relapse prevention. During the assessment session the participant will be asked to define 3 goal-based outcomes (GBOs) [47] for how they hope the intervention will reduce their loneliness, which will then guide the treatment process. During the intervention phase the participants will complete routine outcome measures (ROMs) for each session. This will include the Three-Item Loneliness Scale [34], visual analogue scales (VAS) of mood, anxiety and loneliness and ratings of their goal-based outcomes [48]. The ROMs will be completed via Qualtrics [41] before each session. If participants have not completed the ROMs before their appointment, then they will be completed with the clinician at the start of the session.

Participants will begin the post-intervention phase immediately after the final session of their intervention. During the post-intervention phase participants will be asked to complete the primary outcome measure, Three-Item Loneliness Scale [34], each day for 12 days. They will then complete their post-intervention assessment with the second researcher. Before the assessment they will be asked to re-complete the baseline questionnaires in addition to the parent and child-report versions of the Experience of Service Questionnaire [39] and a questionnaire asking whether COVID-19 or any other events have affected them during the intervention period. The family will be given a £25 voucher for completing the post-intervention assessment. A letter will be sent to their General Practitioner (GP) informing them of their participation in the research study has finished.

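### The stated minimum of 12 observations per phase is only an average in the intervention phase, where the primary scale is rated once per session and no lower limit on sessions is given

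*Protocol article*

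**What the plan says.** All of this is in the protocol article, Methods, Procedure.

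- **Claim.** After listing the baseline lengths, the section says: "The decision to have a minimum of 12 observations per phase meets the requirements for guidelines and standards". It adds that this "will allow for sufficient power for Tau-U analysis". No effect size, significance level or power figure is given.
- **Baseline.** Participants are "randomised using a random number generator to one of four different baseline lengths (12 days, 19 days, 26 days or 33 days"), with one rating of the scale per day.
- **Intervention.** "Each family will receive (on average) 12 sessions of CBT for loneliness in children and young people". The sessions are laid out, where possible, as three blocks of four. On measurement: "During the intervention phase the participants will complete routine outcome measures (ROMs) for each session". "This will include the Three-Item Loneliness Scale", which is the primary outcome. A form not completed beforehand is filled in with the clinician when the session starts.
- **Post-intervention.** The scale is completed "each day for 12 days".

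Data analysis, Primary outcome measure, applies Tau-U to baseline against intervention and to baseline against post-intervention, with a weighted average over all cases.

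**The concern.** A minimum is a property that every participant's phase should have. In the intervention phase the number of primary-outcome ratings equals the number of sessions, and that number is described only by its average. The justification for the design and the schedule therefore disagree before any data are lost.

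This matters because the 12-per-phase figure is the only support given for two claims: that the design meets published standards, and that Tau-U has enough power. Tau-U on these phases is the primary statistical analysis, and Study design says that effects are to be tests for individual participants. The count in each participant's phase is therefore the relevant quantity.

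**Working it through.** **1. Ratings that the schedule gives per participant** (phase length × frequency)

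| Phase | Schedule | Ratings |
|---|---|---|
| Baseline | 12, 19, 26 or 33 days, daily | 12, 19, 26 or 33 |
| Intervention | one per session, 12 sessions on average | 12 on average, no stated lower limit |
| Post-intervention | 12 days, daily | 12 |

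The figure of 12 is reproduced as a scheduled minimum for baseline and post-intervention. It is not reproduced for the intervention phase. If the realised average is 12, all participants reach 12 only when each has exactly 12 sessions; one participant above 12 means that another is below. How many would fall below cannot be derived from the document. If session counts were roughly normal around 12 with an SD of 1, 2 or 3 (assumption), the share below 12 would be 31%, 40% or 43%.

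**2. Slack in the 12-day phases.** With 12 scheduled ratings, one missed day leaves 11. The document gives no completion rate. If days are independent with completion rate c, the chance of all 12 is c^12:

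- c = 0.99: 0.89
- c = 0.95: 0.54
- c = 0.90: 0.28
- c = 0.80: 0.07

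The longer baselines have ample slack: even at c = 0.80, the 19-day baseline yields 12 or more ratings with probability 0.977.

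**3. What a shortfall costs.** The power claim has no stated inputs and cannot be reproduced. As an illustration, take Tau for non-overlap without baseline-trend correction, independent readings and two-sided 5% (all assumptions). Under no effect, SE = √[(nA + nB + 1) / (3·nA·nB)], and the critical |Tau| is 1.96 × SE.

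| Baseline vs later phase | SE | Critical Tau (absolute) |
|---|---|---|
| 12 vs 12 | √(25/432) = 0.241 | 0.47 |
| 12 vs 11 | √(24/396) = 0.246 | 0.48 |
| 12 vs 10 | √(23/360) = 0.253 | 0.50 |
| 12 vs 8 | √(21/288) = 0.270 | 0.53 |
| 26 vs 8 | √(35/624) = 0.237 | 0.46 |
| 33 vs 8 | √(42/792) = 0.230 | 0.45 |

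In a simulation of the corresponding rank test (4,000 runs, independent normal readings, assumed true Tau of 0.6), power was 0.77 at 12 vs 12, 0.70 at 12 vs 10 and 0.67 at 12 vs 8.

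One missed day therefore costs almost nothing. A clearly shorter intervention phase matters mainly for participants with the shortest baseline. With 26 or 33 baseline days, even 8 later ratings give a lower threshold than 12 vs 12.

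**The case against.** The sentence describes a design decision and directly follows the baseline lengths, so it can fairly be read as a scheduled minimum. On that reading the baseline and post-intervention phases are correctly described, and missed entries are a matter of compliance that may be handled in a document not shown. This stands: the two 12-day phases lack slack, but they do not contradict the claim.

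The protocol also limits losses. A forgotten session form is completed at the session, daily text reminders are described for the baseline, and completion of measures and session attendance are feasibility outcomes. The three blocks of four show that 12 is the intended session count. This also stands, but the session fallback rescues a missed form, not a session that is never held, and an intended count of 12 described as an average is still not a minimum.

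A reader might infer that most participants will have a phase below 12 ratings. The document does not support that. It depends on assumed completion rates and an assumed spread of session counts; at 99% daily completion, 89% of participants would have a full post-intervention phase. A reader might also infer that the design fails the cited standard. The document does not say what that standard requires, so nothing shows that 10 or 11 ratings would fall short of it.

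**Conclusion.** The inconsistency holds for the intervention phase. The plan states a minimum of 12, but the schedule supports 12 on average with no stated lower limit. It needs no assumption about missing data. The two 12-day phases meet 12 as scheduled and have no room for a missed entry.

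The statistical cost is small to moderate and is concentrated in individual tests against the 12-day baseline: a critical |Tau| of 0.48 after one lost rating and 0.53 at 8 ratings, compared with 0.47 at 12 vs 12. Eight is an unfavourable illustration, not a count that the document suggests. These figures assume independent readings, no trend correction and two-sided 5%. The weighted average across cases is less affected. What is established is that the property supporting the standards and power claims is not secured, not that either claim is false.

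**What to change.** **Preferred.** In the intervention phase, also collect the Three-Item Loneliness Scale on fixed calendar days, for example weekly, through the Qualtrics forms and text prompts already in use. Choose the frequency so that at least 12 ratings do not depend on how many sessions are held. This changes measurement only and leaves the number of sessions to clinical judgement.

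After the intervention, allow a few spare daily ratings. With 14 scheduled days, for example, the chance of at least 12 ratings is c^14 + 14(1−c)c^13 + 91(1−c)²c^12:

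- c = 0.95 (assumed): 0.488 + 0.359 + 0.123 = 0.97, compared with 0.54 for 12 of 12
- c = 0.90 (assumed): 0.229 + 0.356 + 0.257 = 0.84, compared with 0.28

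Keep the 12/19/26/33-day stagger, since lengthening only the shortest baseline would break its even 7-day steps. The 12-day baseline then still has no slack, so describe its 12 as scheduled ratings.

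The cost is a set of extra brief ratings over the intervention period and a post-intervention assessment that may fall a few days later.

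**Otherwise.** Replace *minimum* with *planned number*, say that it is an average of 12 in the intervention phase, and restate the standards and power claims for the counts that the schedule supports, with the inputs behind the power statement. This costs only a change of wording.

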## Methods

### Study design

The efficacy of CBT for loneliness in children and young people will be evaluated through a randomised multiple-baseline single-case experimental design (SCED) [28–30]. The design consists of AB+ post-intervention, where A is the baseline phase, B is the intervention phase and then a post-intervention phase. In the SCED approach participants are repeatedly assessed on at least one independent variable, in this case self-reported loneliness on the Three-item Loneliness Scale [34], across each phase of the intervention. This repeated measurement and within subject replication is then used to test the effects of the intervention for individual participants [28, 30]. Multiple-baseline SCEDs are a controlled experimental approach, with multiple-baselines protecting against threats to internal validity [40].

The construction of this SCED trial and the reporting of the results will be in accordance with the Single-Case Reporting Guidelines in Behavioural Intervention (SCRIBE) [30].

The study has received ethical approval from Royal Holloway, University of London on 22.03.2021 (ethical approval number: 2489). The study was registered with ClinicalTrials.gov on 07.12.2021 (registration number: NCT05149963).

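### Ratings tied to front-loaded sessions make the individual baseline-versus-intervention Tau-U test insensitive to gradual change, and the power statement does not support that comparison

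*Protocol article*

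**What the plan says.** The Three-Item Loneliness Scale is collected daily in the baseline phase and daily for 12 days after treatment (Procedure). In between, collection follows the sessions: "During the intervention phase the participants will complete routine outcome measures (ROMs) for each session", and "The ROMs will be completed via Qualtrics [41] before each session". The session plan is "Where possible the first 4 sessions will take place bi-weekly, the second 4 sessions weekly and the final 4 sessions fortnightly". The number of sessions is an average: "Each family will receive (on average) 12 sessions of CBT for loneliness in children and young people". On content, "For all participants the first two sessions will be focussed on assessment and then formulation".

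Participants are randomised to "one of four different baseline lengths (12 days, 19 days, 26 days or 33 days". The same section calls 12 observations per phase a minimum and says that this number "will allow for sufficient power for Tau-U analysis". It gives no effect size, significance level or target power.

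The Aims and objectives name two primary comparisons: baseline versus intervention and baseline versus post-intervention. Under Data analysis, Tau-U is applied to both, with a weighted average across cases, alongside visual inspection. The Study design section says that the repeated measurements are "used to test the effects of the intervention for individual participants".

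**The concern.** Because the rating schedule copies the session schedule, readings are densest when little change can have built up and sparsest when most of it should be visible. Each rating precedes its session, so the first reading is taken before any therapy. The first two sessions are assessment and formulation, so the first three readings precede every elective module. Tau-U gives every baseline–intervention pair the same weight, so these early readings pull the statistic towards zero.

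Baseline versus intervention is also the only primary comparison made while other participants are still in baseline. The longest baseline is 33 days and all baselines start together, so nobody is still in baseline when the first participant reaches the post-intervention phase about 12 weeks into therapy. A non-significant individual result here could be read as no effect, because the protocol tells the reader that power is sufficient.

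There is a smaller inconsistency as well. Twelve observations is called a minimum per phase, yet the number of intervention readings equals the number of sessions, which is 12 only on average.

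**Working it through.** **1. Timing.** Bi-weekly is read as twice weekly, because the same sentence uses fortnightly separately. Session days are then 0, 3.5, 7, 10.5, 14, 21, 28, 35, 42, 56, 70, 84.

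- Readings before day 14: 4 of 12 = 33% (5 if day 14 itself is counted).
- Mean reading day: 371/12 = 30.9, and 30.9/84 = 37% of the phase. Even spacing gives 50%.
- If the fortnightly gap starts one session earlier (last four sessions on days 49, 63, 77, 91): 399/12 = 33.25, and 33.25/91 = 37%.

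**2. What 12 intervention readings can detect.** The protocol gives no power figure to reproduce. For Tau comparing nA baseline with nB intervention readings, without baseline-trend correction, SE = √[(nA + nB + 1)/(3·nA·nB)]. The critical value is 1.96·SE (two-sided 5%), and the Tau needed for 80% power is (1.96 + 0.84)·SE. For an immediate step of d SDs, Tau = 2Φ(d/√2) − 1.

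| nA | SE (nB = 12) | Critical Tau | Tau for 80% power | Equivalent step (SD) |
|---|---|---|---|---|
| 12 | √(25/432) = 0.241 | 0.47 | 0.67 | 1.39 |
| 19 | √(32/684) = 0.216 | 0.42 | 0.61 | 1.21 |
| 26 | √(39/936) = 0.204 | 0.40 | 0.57 | 1.12 |
| 33 | √(46/1188) = 0.197 | 0.39 | 0.55 | 1.07 |

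If a participant has only 10 sessions, the Tau needed for 80% power rises to between 2.80·√(44/990) = 0.59 (33-day baseline) and 2.80·√(23/360) = 0.71 (12-day baseline).

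**3. Gradual change.** These inputs are assumed and are not in the protocol: SD 1.5 points, independent readings, scores rounded to 0–12, and a linear gain reaching 1.5 SD (1.5 × 1.5 = 2.25 points) at the last session. Expected Tau is about 0.28 on the session schedule and 0.37 if evenly spaced. A normal approximation gives Φ(0.28/0.241 − 1.96) = Φ(−0.80) = 21% for the 12-day baseline and Φ(0.28/0.197 − 1.96) = Φ(−0.54) = 29% for the 33-day one. Simulation gives:

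| Rating schedule | 12-day baseline | 33-day baseline |
|---|---|---|
| Session-tied (as planned) | about 19% | about 28% |
| Weekly, fixed days | about 34% | about 51% |
| Twice weekly, fixed days | about 45% | about 71% |

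A separate simulation with SD 2 and a 91-day span gave 19–28% for 1.5 SD and 30–47% for 2 SD on the session schedule. With baseline-trend correction, the 1.5 SD figure was 18–20%.

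**4. The other comparisons.** If the 1.5 SD gain is held, baseline versus post-intervention (12 daily readings) is a 1.5 SD step, with power about 92–98%. For the weighted average over 6 cases the SE is about 0.087, so power for the gradual 1.5 SD gain is Φ(0.28/0.087 − 1.96) = Φ(1.26) = 90%. With 8 cases the simulated figure is 97%.

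**The case against.** A reader might infer that the trial lacks power for individual participants, or that someone who improves slowly will usually be reported as unchanged. The documents support neither. Baseline versus post-intervention is an equal primary comparison for each participant, and it would usually detect the same gain if it is held. The pooled estimate is well powered in the same scenario. Visual inspection also covers trend and slope, where gradual change would show. Nor can the power statement be called false as a figure: it names no effect size, alpha or target, and does not say that it refers to individual tests.

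The assumed shape also matters. Therapy is front-loaded too. If benefit builds per session delivered rather than per calendar day, the readings are evenly spaced in dose, and power for 1.5 SD is about 36–52%. For an immediate 1.5 SD step it is 91–99% without trend correction. These points stand, and they confine the problem to individual baseline-versus-intervention tests under gradual change. Even the per-session shape stays below 80%.

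Two objections bear on the remedy. First, other participants remain in baseline for at most 33 − 12 = 21 days after the first one starts therapy. The session schedule gives 5 readings before day 21 of therapy, and weekly ratings would give 3. Twice-weekly ratings (days 0, 3.5, 7, 10.5, 14, 17.5) give 6, which is why they are preferred. Second, no calendar schedule considered here reaches 80% for the gradual 1.5 SD gain, so the remedy improves sensitivity without making the power claim true.

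Finally, if bi-weekly meant every two weeks, the phase would last about 18 weeks and the front-loading would disappear. The separate use of fortnightly makes that reading unlikely.

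**Conclusion.** The point holds for the individual baseline-versus-intervention comparison. One third of the readings come from the first two of roughly 12 to 13 weeks, and the mean reading falls at 37% of the phase. For a gradual 1.5 SD gain, individual power is about 19–28%, roughly half or less of what fixed-day ratings would give. The statement of sufficient power is unsupported for this comparison and not met for gradual change. It is not contradicted for baseline versus post-intervention or for the pooled average.

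The timing figures rest only on the protocol's schedule and the twice-weekly reading. The power figures also rest on the assumed SD, effect shape and independence. Daily autocorrelation of 0.3 leaves the ordering of the schedules intact, but raises the type I error of the test to about 7–9%, so power under autocorrelation should not be taken at face value. Separately, the stated minimum of 12 observations is not guaranteed in the intervention phase.

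**What to change.** 1. Collect the Three-Item rating on fixed calendar days throughout the intervention phase, preferably twice weekly, through the Qualtrics and SMS prompts already used in baseline. Use these ratings in Tau-U for baseline versus intervention. Keep the session measures as process data. Session timing does not change.
2. Qualify the power statement by comparison and baseline length. If 12 intervention readings are kept, critical |Tau| is about 0.47 (12-day baseline) to 0.39 (33-day), and 80% individual power needs an immediate step of roughly 1.4 down to 1.1 SD, assuming independent readings and no baseline-trend correction. If the denser schedule is adopted, recompute these for the new number of readings.
3. State that a non-significant individual baseline-versus-intervention result is not evidence of no effect.
4. Reconcile the minimum of 12 observations per phase with a session count that is 12 on average. Calendar prompts remove the dependence.

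Cost: about 25 three-item ratings per participant over 84 days if twice weekly, or 13 if weekly, in a study that already asks for 24 to 45 daily ones (12 to 33 in baseline plus 12 afterwards). Some will be missed, because completing an overdue rating with the clinician at the session does not cover calendar-day ratings. The stated power will also look less favourable.

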#### Feasibility and satisfaction measures

The proportion of our minimum recruitment target of 6 participants that we achieve will be reported. Successful completion of 6 participants will indicate that the recruitment protocol is feasible. The proportion of participants retained, defined as completing both the baseline and intervention assessments will be reported; with an 80% retention rate indicating that the research protocol is feasible, based on previous studies [71]. We will also report the proportion of appointments attended across all participants. The key themes identified in the Experience of Services Questionnaire [39] and the questionnaire assessing the impact of COVID-19 or other events on the child’s loneliness will also be reported. Acceptability will be indicated by 80% positive responses on the Experience of Services Questionnaire [39].

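### During the intervention phase the primary outcome is requested only around sessions, so an appointment missed or rebooked on a bad day can leave no reading for that day, and selective loss would tilt the baseline versus intervention Tau-U towards benefit

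*Protocol article*

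**What the plan says.** All of the following is in the Protocol article.

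- **Baseline (Methods, Procedure).** "During the baseline phase participants will be asked to complete the Three-Item Loneliness Scale [34] each day via Qualtrics". Each participant is randomised to "one of four different baseline lengths (12 days, 19 days, 26 days or 33 days". In the same paragraph: "SMS message reminders will also be sent to the young people and their parent/carers each day".
- **Intervention (Procedure).** "During the intervention phase the participants will complete routine outcome measures (ROMs) for each session". On their content: "This will include the Three-Item Loneliness Scale [34], visual analogue scales (VAS) of mood, anxiety and loneliness". The stated route is Qualtrics, ahead of the session. The only back-up is this: "If participants have not completed the ROMs before their appointment, then they will be completed with the clinician at the start of the session". No rating is described between sessions, or for a session that does not take place.
- **Post-intervention (Procedure).** The scale is again due daily, for 12 days.
- **Analysis (Data analysis, Primary outcome measure).** Tau-U is applied to baseline versus intervention and to baseline versus post-intervention, with a weighted average over cases.
- **Attendance (Feasibility and satisfaction measures).** "We will also report the proportion of appointments attended across all participants". No expected rate is given.

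**The concern.** The rule that decides whether a reading is requested changes at the phase boundary. At baseline a rating is due on every calendar day. In the intervention phase it is due because a session is due, and the safety net for an uncompleted form works only if the young person attends. A missed appointment with no form completed beforehand leaves nothing. A rebooked one yields a score from a later day on which the young person was able to attend; this restores the count but not the reading from the original day.

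Attendance in lonely, low or anxious young people may depend on how they feel. If it does, high scores are thinned out on one side of a primary contrast. Tau-U compares all pairs of baseline and intervention readings and can adjust for baseline trend, but it has no means of allowing for readings that are selectively absent. Staggered baselines do not help either: the change in rule falls at each participant's own phase change, so the same artefact would recur from case to case and look like replication.

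The point is which readings are absent, not how many are planned or how they are spaced.

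**Working it through.** **The protocol's own figure.** The Procedure section states a minimum of 12 observations per phase. The shortest baseline gives 12 daily ratings, the intervention gives 4 + 4 + 4 = 12 session ratings, and post-intervention gives 12 daily ratings. The figure is reproduced, but without slack: in a 12-session course, one lost and unreplaced reading goes below the minimum. If sessions are missed independently with probability q and each miss costs a reading, the chance of all 12 is (1 − q)^12, which is 54%, 28% and 7% for q = 0.05, 0.10 and 0.20. These values of q are assumptions.

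**Bias with no true effect.**

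Inputs from the protocol: 6 to 8 participants; baselines of 12, 19, 26 and 33 days; 12 intervention readings; scale 0 to 12, higher meaning lonelier.

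Assumptions not in the protocol: independent daily scores, mean 7 and SD 1.5, rounded and kept within 0 to 12, with the same distribution in both phases; no baseline-trend correction; the miss probabilities in the table.

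For a case with n_A baseline and n_B intervention readings:

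- Tau = (pairs with A > B − pairs with A < B) / (n_A × n_B), so a positive value means improvement.
- Var(Tau) = (n_A + n_B + 1) / (3 × n_A × n_B).
- Pooling weights are 1/Var. A trial counts as a false improvement if the pooled z exceeds 1.96 (nominal 2.5%).

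The overall miss rate is one third of the bad-day probability plus two thirds of the other. For 0.4 and 0.1 this is 0.133 + 0.067 = 0.20.

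| Miss probability, loneliest third / other days | Missed overall | Mean Tau | False improvement, 6 to 8 cases |
|---|---|---|---|
| 0.1 / 0.1 (unrelated to loneliness) | 10% | 0.00 | about 2% |
| 0.3 / 0.1 | 17% | +0.05 | 7–9% |
| 0.4 / 0.1 | 20% | +0.08 | 12–16% |
| 0.5 / 0.1 | 23% | +0.11 | 20–27% |

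A second simulation with mean 8 and SD 2 gave the same Tau values and similar error rates (7–9%, 12–15% and 20–27% for the last three rows).

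**Relaxing the assumptions.** The first, second and fourth rows below start from 0.4 / 0.1.

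| Change | Mean Tau | False improvement, 6 to 8 cases |
|---|---|---|
| Half of the missed sessions already rated online | about +0.04 | about 6% |
| Baseline ratings also skipped, 0.3 on bad days / 0.1 on others | +0.03 | 4–5% |
| Lower miss rate, 0.2 / 0.05 (10% overall) | +0.04 | 5–6% |
| Same selective skipping in both phases | 0.00 | about 2% |

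The direction is therefore clear once loss is selective and heavier in the intervention phase. The size depends entirely on the assumed pattern.

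**The case against.** Three stronger readings are tempting, and the documents support none of them.

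*A missed appointment always means a missing score.* It does not. The main route is the online form before the session, and the clinician is only the back-up. Someone who completes the form and then stays away leaves a reading. What stands is that someone too low to attend may also not have completed the form, and no other route is described.

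*The trial will be biased towards CBT.* The protocol gives no attendance rate and no evidence that attendance follows loneliness, and remote sessions remove travel as a barrier. Baseline ratings are unsupervised, so they too may be skipped on bad days, which would push Tau the other way. The upper error rates need strong selection, complete baseline data and no forms completed in advance, all together. This stands, and it is why the size is given as a range.

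*The primary outcome as a whole is compromised.* Baseline versus post-intervention uses daily ratings in both phases and does not depend on attendance. Visual inspection is also planned, and completion of measures is a feasibility outcome. This stands as well. It limits the point to one of the two primary contrasts.

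It can also be said that a cancelled session is operational detail for a fuller protocol or an analysis plan. Handling of missing values may be. But the article itself fixes when the primary outcome is requested, and an analysis plan cannot recover readings that were never requested.

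**Conclusion.** The point holds as a conditional weakness in the rating schedule. Whether an intervention-phase reading exists can depend on attendance, unless the form was completed beforehand; at baseline it cannot. If sessions are missed more often when loneliness is high, baseline versus intervention leans towards benefit.

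Under the assumed selective patterns with a complete baseline, Tau is shifted by about +0.05 to +0.11 and false pooled improvement is about 7 to 27%, against about 2%. Allowing for forms completed in advance, for skipped baseline ratings or for about 10% missed sessions reduces this to about +0.03 to +0.04 and 4 to 6%. It vanishes if loss is unrelated to loneliness or equally selective in both phases. All miss rates, and the independence of daily scores, are assumptions. This is a worthwhile and cheap improvement, not a defect that invalidates the trial.

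**What to change.** In the Procedure section, at the description of the intervention-phase measures:

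1. Make the Three-Item rating due by Qualtrics link, with the same SMS reminder as at baseline, on every originally scheduled session date, whether or not the appointment is kept.
2. State that a rebooked session adds a reading and does not replace the one due on the original date.
3. Use all scheduled-date readings in the baseline versus intervention Tau-U, and show the attended-only result as a sensitivity analysis.
4. Report missing ratings by phase, so that a reader can judge whether loss was one-sided.

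The cost is a change of wording, one automated message using tools already in place, and about a minute of rating per missed session. Therapy is unchanged. The fix lessens the dependence on attendance but does not guarantee a response: a young person who avoids the session may also ignore the link. If every scheduled-date rating is obtained, the no-effect simulation returns Tau of about 0.00 and a false-improvement rate of about 2%.
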